### Sample Size Calculation

The sample size was estimated based on the planned analyses of incident myopia over the 3-year follow-up in the prospective cohort, with prespecified 1:1 matching in the nested case-control component. Published epidemiological studies indicate that myopia prevalence is relatively low in preschool-aged children but increases rapidly after school entry. For example, Lan et al [18] reported that the prevalence of myopia among 3-year-old children was <2.5%, whereas He et al [19] reported a prevalence of 5.9% among 6-year-old children and an average prevalence of approximately 36% among primary school students in Guangzhou.

On the basis of these data and the anticipated number of incident myopia cases during follow-up, the minimum required cohort size was estimated to be 915 participants to support multivariable analyses and the prespecified nested case-control comparisons. Allowing for an anticipated 10% loss to follow-up, the final target sample size was increased to 1006 participants. This cohort size is expected to generate a sufficient number of incident myopia cases during follow-up to allow for 1:1 risk-set matching and adjustment for key confounders.

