### Data Collection and Follow-Up

This study does not involve any intervention. All procedures are observational and consist of standardized ophthalmic examinations and questionnaire-based assessments conducted at baseline and at each annual follow-up visit. The following biological parameters were measured annually in children in the cohort: visual acuity, cycloplegic refraction, AL, ACD, CR, ocular position, fundus, height, weight, and other parameters.

First, visual acuity was assessed using the Early Treatment Diabetic Retinopathy Study visual acuity chart at a distance of 4 m, with the 1.0 line at eye level. Visual acuity was assessed monocularly, with one eye covered without applying pressure while the other eye was tested. Measurements were performed in a right-to-left sequence. The number of correctly identified letters was determined by reading optotypes from top to bottom.

Second, cycloplegic refraction was performed using 1% cyclopentolate hydrochloride. Initially, 1 drop of 0.4% oxybuprocaine hydrochloride (as topical anesthetic) was instilled. Following a 3-minute interval, 1% cyclopentolate hydrochloride eye drops were administered at 5- to 10-minute intervals for 3 consecutive doses. Pupillary diameter and light reflex were assessed 30 minutes after the final instillation. Complete cycloplegia was defined as pupillary dilation ≥6.0 mm and absence of pupillary light reflex (grade 0 on the standardized light reaction scale). Participants meeting these criteria underwent automated refraction using a calibrated autorefractor (Nidek ARK-1), with triplicate measurements obtained under mesopic conditions (3 cd/m²).

Third, ocular biometric parameters, including AL, CR, and ACD, are measured using an optical interferometric AL meter (AL-Scan, Nidek Co, Ltd). The AL to CR ratio is calculated as AL-to-CR=AL/mean CR. The device automatically obtained multiple measurements and reported averaged values.

Fourth, eye position was assessed using masking-demasking and alternating masking methods to screen for strabismus. The direction of ocular movement was assessed to determine whether the participant had strabismus or occult strabismus.

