**Figure 2. F2:**
[figure not shown]
The basic statistical design plan of the study.

Secondary analyses will examine longitudinal changes in ocular biometric parameters, including AL, ACD, CR, and the AL to CR ratio. These analyses will be performed using linear mixed-effects models to account for within-subject repeated measurements over time. Participants will be grouped according to baseline levels of physiological hyperopia, and sensitivity analyses will be conducted accordingly.

Sensitivity analyses will be performed by stratifying participants according to baseline physiological hyperopia levels (eg, age-specific categories) and by evaluating alternative analytic-eye definitions (right eye only vs both eyes using appropriate correlation structures).

All statistical analyses will be performed using SPSS (version 26.0; IBM Corp), RStudio (version 1.4; Posit PBC), and MATLAB (version 2021a; MathWorks Inc). A 2-sided *P*<.05 will be considered statistically significant.

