### Limitations

This study has several limitations that should be considered when interpreting the findings. First, although the cohort is relatively large and well characterized, participants were recruited from a single district in Beijing. Therefore, the findings may not be fully generalizable to children in other regions with different socioeconomic, educational, or environmental contexts. Second, this study is observational in nature. While the prospective design and nested case-control analyses strengthen temporal inference, causal relationships between physiological hyperopia–related exposures and myopia onset cannot be definitively established, and residual confounding may persist despite multivariable adjustment. Third, physiological hyperopia and related environmental exposures were assessed at discrete annual time points. More frequent measurements might better capture short-term fluctuations in refractive development and behavioral factors. In addition, some exposure information was collected via parent-reported questionnaires, which may be subject to recall or reporting bias. Finally, although standardized cycloplegic refraction and ocular biometry were used, analytic decisions such as eye selection and categorization of physiological hyperopia may influence effect estimates. However, sensitivity analyses were conducted to assess the robustness of the findings to these analytic choices.

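### The secondary mixed models name only grouped baseline hyperopia, although refraction is measured continuously; a continuous term would keep information at almost no cost

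*Protocol article*

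**What the plan says.** The Statistical Analysis Plan section of the protocol article introduces the secondary analyses thus: "Secondary analyses will examine longitudinal changes in ocular biometric parameters, including AL, ACD, CR, and the AL to CR ratio". It names the model: "These analyses will be performed using linear mixed-effects models to account for within-subject repeated measurements over time". The next sentence gives the only form in which baseline hyperopia appears in this paragraph: "Participants will be grouped according to baseline levels of physiological hyperopia, and sensitivity analyses will be conducted accordingly".

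A separate paragraph describes the sensitivity analyses: "Sensitivity analyses will be performed by stratifying participants according to baseline physiological hyperopia levels (eg, age-specific categories"), together with a change of analysed eye (right eye only, or both eyes with a correlation structure).

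The Data Collection and Follow-Up section shows that the underlying measurement is continuous: "Participants meeting these criteria underwent automated refraction using a calibrated autorefractor (Nidek ARK-1), with triplicate measurements obtained under mesopic conditions".

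The Limitations section accepts that "analytic decisions such as eye selection and categorization of physiological hyperopia may influence effect estimates" and points to the sensitivity analyses as the safeguard.

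**The concern.** Grouping a continuous covariate treats all children within a band as alike, puts a step at each boundary, and makes the estimated differences depend on where the boundaries fall. Here it saves nothing, because every child's dioptre value is already collected.

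The safeguard named in the Limitations section does not cover the problem. Stratifying again by baseline level keeps the categorization, and changing the analysed eye does not touch it. As described, no analysis shows whether the results hold once the categories are removed.

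At stake are precision for the weaker associations between baseline hyperopia and later eye growth, and the ability to show the shape of that relation. The primary outcome, incident myopia, is analysed by conditional logistic regression and is not part of this point.

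**Working it through.** **Inputs from the article**
- Minimum cohort size (Sample Size Calculation): "the minimum required cohort size was estimated to be 915 participants". The target is 1006 after a 10% allowance for loss. Check: 915 × 1.10 = 1006.5, which matches 1006 when cut down; 915 / 0.90 would give 1017. This has no bearing on the point except to supply n.
- Children remaining after 10% loss: 1006 × 0.90 = 905.4, so n = 905.
- Two-sided 5% test (Statistical Analysis Plan).
- Number of groups, cut-points, mean and SD of baseline refraction: not given. The article states no figure for information loss, so there is none to reproduce.

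**Assumptions**
- Baseline spherical equivalent is normal and its relation to biometric change is linear.
- Groups are equal-sized unless stated otherwise.
- Power uses a single-observation correlation r between baseline refraction and change, as an approximation to the repeated-measures model.

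**Step 1. Information kept.** For a standardised covariate cut into groups with shares p_g and group means m_g, the share of information kept is the between-group variance, Σ p_g m_g².
- 2 equal groups: means ±0.798, so 0.798² = 0.637 kept, 36% lost (exactly 1 − 2/π).
- 3 equal groups: means −1.091, 0 and 1.091, so (2/3) × 1.091² = 0.793 kept, 21% lost.
- 4 equal groups: means ±1.271 and ±0.325, so (1.271² + 0.325²)/2 = 0.861 kept, 14% lost.

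**Step 2. Sensitivity of that range.**
- 5 equal groups lose 10%.
- A 20/80 split has means −1.400 and 0.350: 0.2 × 1.400² + 0.8 × 0.350² = 0.490 kept, 51% lost.
- A heavy-tailed covariate (t with 5 df, by simulation) loses 46%, 31% and 24% with 2, 3 and 4 equal groups.

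**Step 3. Power.** Noncentral F with noncentrality λ = n·r²/(1 − r²). For groups, r² is first multiplied by the share kept. A 1-df linear term has 80% power at r = 0.0928, where λ = 905 × 0.00862 / 0.99138 ≈ 7.87.

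| Test at r = 0.0928 | df | Power |
|---|---|---|
| Continuous, linear term | 1 | 80% |
| 2 groups | 1 | 61% |
| 3 groups, omnibus | 2 | 60% |
| 4 groups, omnibus | 3 | 57% |
| 3 groups, trend with optimal scores | 1 | 70% |
| 4 groups, trend with optimal scores | 1 | 74% |
| Spline, joint test | 2 | 71% |
| Spline, joint test | 3 | 64% |

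Where the linear term has 90% power (r = 0.1072), omnibus group tests have 73%, 73% and 71% with 2, 3 and 4 groups. At r = 0.20 every one of these group tests exceeds 99%, as does the linear term.

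**Step 4. Reading the table.** Part of the gap between 80% and 57 to 61% is information lost by grouping, and with 3 or 4 groups part is the extra degrees of freedom of an omnibus test. A trend test across groups recovers much of the second part. A joint spline test pays the same kind of df penalty. At equal df the continuous form still does better: 71% against 60% with 2 df, and 64% against 57% with 3 df. The full gain needs a 1-df linear term.

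**The case against.** **The sentence can be read more narrowly.** The grouping clause runs straight on to sensitivity analyses, and the next paragraph defines those as stratification. Nothing says a continuous term is excluded or that the groups are the regressor in the mixed model. This stands in part. A reader might infer that the plan replaces continuous refraction with groups, but the text does not go that far. It supports only that grouping is the one form named and that no continuous term is planned.

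**The article is condensed.** The number of groups and the cut-points may well sit in a fuller plan, and their absence is not the criticism. Age-specific categories also have a rationale, since the Study Design section calls hyperopic reserve age dependent. Both points stand. They do not remove the concern, which is the form of analysis that the article does name.

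**A spline does not recover the whole loss.** If the truth is linear, its joint test has 64 to 71% power, no better than a trend test across 3 or 4 groups (70 to 74%). This stands, and is why the main test should be a linear term with the spline as a check of shape.

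**The study does not ask for a dioptre threshold.** A reader might infer that groups defeat a stated aim of finding critical hyperopia levels. The Abstract speaks of turning points and the Introduction of the timing of transitions; neither sets out to locate a cut-off in baseline dioptres, and the Objective names none. The point should not rest on that aim.

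**These analyses are secondary and largely descriptive.** The Study Design section places the main inference in the nested case-control comparison. This stands and limits the weight of the point.

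**Conclusion.** The point holds in a limited form. For the secondary mixed models the article names only grouped baseline hyperopia, although a continuous measurement exists, and the planned sensitivity analyses do not test the categorization that the article itself says may influence the estimates.

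Under the assumptions listed, the information lost is about 14%, 21% or 36% with 4, 3 or 2 equal groups, and roughly 10% to 51% once five groups or a 20/80 split are allowed. No single figure can be derived from the article, and a non-linear relation would change all of them. The power cost is confined to weak associations: omnibus group tests fall about 19 to 23 points below a linear term that has 80% power, and less if a trend test is used. By r = 0.20 it is negligible. Dependence on cut-points remains at any effect size.

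This is a worthwhile, inexpensive improvement to secondary analyses. It does not call the primary analysis into question.

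**What to change.** In the secondary-analysis paragraph of the Statistical Analysis Plan section, replace the grouping sentence with:

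> In the linear mixed-effects models, baseline cycloplegic spherical equivalent will enter as a continuous linear term with its interaction with time, adjusted for baseline age; a restricted cubic spline (3 to 4 knots) will be used to check the shape. Hyperopia groups will be used for descriptive tables, plots and sensitivity analyses.

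The cost is a change of wording and a few lines of code, with no new data, visits or participants. The Results section says analysis begins only after data collection is complete, so the change can still be prespecified. The small downside is presentation: results appear as a slope, or as contrasts at chosen dioptre values, rather than one estimate per group.

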### Ethical Considerations

Throughout the study, all procedures were in accordance with the Declaration of Helsinki.

The study received ethics approval on April 7, 2024, from the Ethics Committee of Beijing Tongren Eye Center, Beijing Tongren Hospital, (TREC2024-KY034), and was registered on July 5, 2024. In addition to explaining the purpose and methods of the study, the researchers also explained possible side effects and precautions online before each test. Informed consent was obtained before using cyclopentolate eye drops. No financial or material compensation was provided to participants for their participation in this study.

Medical records and datasets will be maintained at Beijing Tongren Hospital. No personal information will be revealed in any public results report. Data will be examined for authenticity before being given to the study statistician. Data will be kept strictly confidential and evaluated by study staff and authorized personnel. All data files will be password protected and stored on a secure server for a minimum of 10 years and disposed of if they are no longer required. If changes are made to the project, they will be published in ClinicalTrials.gov.

## Results

Participant recruitment began on July 10, 2024, and is expected to be completed by December 31, 2026. As of February 2026, recruitment is ongoing. Data analysis will commence after the completion of data collection, and the final results are expected to be published by December 31, 2026.

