### Study Design

This study is a prospective observational study based on an established cohort, with planned nested case-control analyses embedded within the longitudinal follow-up framework. All participants are followed annually using standardized ophthalmic examinations and questionnaires. Incident myopia cases identified during follow-up are used for the primary inferential analyses through risk-set matched nested case-control sampling, while cohort-level and cross-sectional analyses are conducted to describe longitudinal refractive and biometric changes. The primary inferential analyses are conducted using risk-set matched nested case-control sampling focused on incident myopia. The study period spans from January 1, 2024, to December 31, 2026, and the protocol is registered at ClinicalTrials.gov (NCT06498947).

Our research team previously established a prospective cohort of 2109 preschool children, aged 3 to 6 years, through cluster sampling in 22 kindergartens in Haidian District, Beijing, and completed a 3-year follow-up. Building on this established cohort, this study continues prospective follow-up as children transition into school age (6‐9 years), with annual ophthalmic examinations and questionnaire-based assessments.

Although all participants are followed longitudinally, the primary scientific objective of this study is not to model population-average trajectories alone, but to identify factors associated with the transition from physiological hyperopia to incident myopia during this critical developmental window. For this purpose, a prospective nested case-control design was selected as the main inferential strategy within the cohort framework.

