### Study Setting and Participants

This study focuses on school-aged children in Haidian District, Beijing, and includes a 3-year prospective follow-up. As the educational and technological hub of northwest Beijing, Haidian District has a well-established education management system, facilitating research coordination. Furthermore, the high level of parental compliance with myopia prevention measures in the region ensures the successful implementation of long-term follow-up.

Infants typically exhibit a hyperopia of +3.0 to +4.0 D, which transitions into a period of rapid development before the age of 3 years, followed by a slower developmental phase. By approximately 12 years, the process of emmetropization is gradually completed. On the basis of this developmental pattern, this study focuses on school-aged children as the target population. For this study, children aged 6 to 9 years who met the eligibility criteria were invited to continue annual follow-up examinations for an additional 3 years. Figure 1 illustrates the overall participant flow, including cohort enrollment, eligibility assessment, annual follow-up visits, and identification of incident myopia cases for nested case-control analyses. Textbox 1 lists the inclusion and exclusion criteria.

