Data collection was completed annually within the specified time frame, with a total follow-up period of 3 years. To ensure patient adherence and maintain a high long-term follow-up rate, the following strategies were implemented: (1) collaborating institutions had extensive screening experience and a dedicated professional examination team; (2) a personalized refractive profile was established for each child in the cohort, along with a feedback mechanism for results; (3) volunteer certificates were awarded to children participating in the cohort study to enhance their engagement; and (4) an additional clinical coordinator was appointed to conduct detailed telephone communication with families before each annual follow-up, aiming to reduce lost follow-up rates. These measures also support the feasibility and acceptability of long-term follow-up in school-aged children and their families.

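### The stated calendar cannot deliver the stated 3-year follow-up: first recruitment to study end is at most 2.48 years

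*Protocol article*

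**What the plan says.** All references are to the protocol article.

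- **Study Design:** "The study period spans from January 1, 2024, to December 31, 2026".
- **Results:** "Participant recruitment began on July 10, 2024, and is expected to be completed by December 31, 2026". The status given there is "As of February 2026, recruitment is ongoing".
- **Study Setting and Participants:** "children aged 6 to 9 years who met the eligibility criteria were invited to continue annual follow-up examinations for an additional 3 years".
- **Data Collection and Follow-Up:** annual data collection "with a total follow-up period of 3 years". Secondary Outcomes likewise has every outcome assessed yearly over a 3-year follow-up.
- **Sample Size Calculation:** the size rests on "planned analyses of incident myopia over the 3-year follow-up". It gives a minimum cohort of 915, raised to 1006 for 10% loss.
- **Primary Outcome:** a case is a child who is nonmyopic at baseline and develops myopia during follow-up. The examination that serves as baseline is not dated.
- **Results, on timing of analysis:** "Data analysis will commence after the completion of data collection", and "the final results are expected to be published by December 31, 2026".

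**The concern.** These statements cannot all hold. Three years of annual follow-up after recruitment does not fit between the first recruitment date and the study end, and recruitment is allowed to run to the last day of the study.

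The primary analysis is a 1:1 risk-set matched comparison of incident cases with children still at risk, so its precision depends on the number of cases. The Sample Size Calculation relies on the cohort producing enough cases over three years. If the calendar allows less follow-up, the cohort produces fewer cases than that reasoning assumes, and the published account describes a follow-up that the study did not have.

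**Working it through.** **The plan's own figure.** 915 × 1.10 = 1006.5, which the article gives as 1006. (Dividing 915 by 0.90 gives 1017, about 1% more, which does not matter here.) The base of 915 cannot be rebuilt from the article, which prints no incidence, effect size, power or target case count. The check below therefore concerns follow-up time and relative case numbers, not power.

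**Step 1: longest possible follow-up.** Inputs are the recruitment start (July 10, 2024, Results) and the study end (December 31, 2026, Study Design).

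- Days: 174 (rest of 2024) + 365 + 365 = 904.
- Years: 904 / 365.25 = 2.48.
- The first child recruited would reach 36 months on July 10, 2027. A child recruited on December 31, 2026 would do so on December 31, 2029.
- Counting from ethics approval (April 7, 2024) gives 2.73 years, still short of three.

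**Step 2: annual visits available if baseline is the examination at recruitment.**

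| Recruited | Annual follow-up visits by study end |
|---|---|
| July 10 to December 31, 2024 | 2 |
| During 2025 | 1 |
| After December 31, 2025 | 0 |

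Three visits would require entry by December 31, 2023, before recruitment opened. Recruitment was still open in February 2026, so on this reading the last row can contain children.

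**Step 3: effect on expected cases.** The article states no incidence and no accrual pattern, so both are assumed.

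- 3-year incidence *I*: 20%, 30.1% or 36%. The value 30.1% is only the crude difference between the two cited prevalences (36% − 5.9%); it is not a stated incidence.
- Constant annual risk: *h* = 1 − (1 − *I*)^(1/3), giving 7.2%, 11.3% and 13.8%.
- Cases after *k* annual visits: *N* × [1 − (1 − *h*)^*k*], with *N* = 915 for illustration, all taken as nonmyopic at baseline.
- All enrolled by December 31, 2024: *k* = 2 for every child.
- Uniform accrual: 174/904 = 19% with two visits, 365/904 = 40% with one and 40% with none, a mean of 0.79 visits.

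| Assumed 3-year incidence | Cases, full 3 years | Cases, all enrolled by end of 2024 | Cases, uniform accrual |
|---|---|---|---|
| 20% | 183 | 126 (−31%) | 51 (−72%) |
| 30.1% | 275 | 194 (−29%) | 79 (−71%) |
| 36% | 329 | 235 (−29%) | 96 (−71%) |

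The percentage losses do not depend on *N* and hardly depend on the incidence. They depend on accrual.

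**Step 4: analysis and publication.** Analysis starts only after data collection is complete, and publication is due by December 31, 2026. If recruitment runs to that date, data collection cannot end before it, and no time is left for analysis or publication.

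**The case against.** The strongest defence is that this is continued follow-up of an assembled cohort of 2109 children whose earlier 3-year follow-up is complete. Recruitment may then mean renewed consent or continuing data collection, and the last preschool examination may be the nonmyopic baseline. Rounds in 2024, 2025 and 2026 would give three intervals at risk, and a child who consents again in 2026 could be an incident case. The Primary Outcome section does not rule this out, and the participant flowchart is not available here. But the article nowhere says it, and Data Collection and Follow-Up lists baseline separately from the annual visits. Nor does it rescue the promise of three additional years after invitation. What stands is that the limit of two visits and the exclusion of late entrants are conditional on a recruitment baseline.

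A second defence is that three years means three calendar rounds. From a recruitment baseline in 2024 that still leaves two intervals, and the wording about additional years speaks against it.

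A reader might also infer more than the documents support:

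- **That late entrants can never become cases.** This is true only if baseline is the examination at recruitment.
- **That about 71% of cases will be lost.** That needs uniform accrual, and no accrual pattern is given. Accrual from an existing cohort may be much faster.
- **That unequal follow-up biases the primary comparison.** Risk-set matching at the same time point with conditional logistic regression accommodates unequal time at risk.
- **That a given amount of power is lost.** The article prints no power or effect size, so this cannot be computed.
- **That late entrants age out of the 6-to-9 range.** The dates of the earlier cohort are not given.
- **That publication necessarily falls on the last day of data collection.** The article gives no end date for data collection, and the dates for recruitment and publication are outer limits. The conflict arises if recruitment uses its full window.

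**Conclusion.** The point holds as an internal contradiction that follows from the article's own dates. The longest follow-up from recruitment is 904 days (2.48 years), so the stated three years cannot be completed by any recruited child, and the sample size rests on a period that the calendar does not provide.

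On the recruitment-baseline reading, and assuming constant annual risk and a 3-year incidence of 20% to 36%, the shortfall in expected cases is at least about 29% to 31%. That is the most favourable case, with everyone enrolled by December 31, 2024. The 71% to 72% under uniform accrual only shows how sensitive the result is to late entry. The consequence is fewer cases and wider intervals; the odds ratios themselves are not made invalid.

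**What to change.** **First, reconcile the text.** The places to align are the Abstract, Study Design, Study Setting and Participants, Sample Size Calculation, Secondary Outcomes, Data Collection and Follow-Up, and Results. State which examination is the nonmyopic baseline. State whether recruitment means new enrolment, renewed consent or continuing data collection.

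**Then choose one option.**

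- **A. Keep the December 31, 2026 cut-off.** Describe follow-up as the number of annual visits achievable (up to two from a recruitment baseline). Include in the risk sets only children with at least one post-baseline visit. Restate the expected number of incident cases in Sample Size Calculation.
- **B. Move the study end** in the protocol and the registry so that the stated 3-year follow-up can be completed.

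**In both cases,** set an administrative censoring date and place analysis and publication after data collection ends.

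**Cost.** Either option needs a protocol and registry amendment. Option A means a less favourable stated follow-up and case count; option B means a later end date.
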